#### Biomechanical Analysis

In addition to completing the functional and subjective outcome measures during visits 3 to 5, a subset of 30% (30/100) of the participants will also undergo gait analysis during these visits. Biomechanical gait analysis will include kinetic and kinematic evaluation of level ground walking at 3 speeds and kinematic evaluation of incline and decline ambulation at a self-selected speed. The purpose of these sessions is to collect joint angles, forces, torques, and powers while participants use each ankle-foot device.

#### Gait Laboratory Instrumentation

Gait analysis will be performed at the Veterans Integrated Service Network 2 Biomechanics Research for the Advancement of Veteran Outcomes Laboratory at VANYHHS, the Biomechanics Laboratory at WRNMMC, and the Rehabilitation and Biomechanics Laboratory at JAHVH. The Veterans Integrated Service Network 2 Biomechanics Research for the Advancement of Veteran Outcomes Laboratory is a 1440-square foot space comprising an 11-camera motion capture system (Qualisys Inc) with 4 multiaxis force platforms (AMTI Inc). At WRNMMC, the Biomechanics Laboratory is an 1800-square foot space comprising an 18-camera motion capture system (Qualisys Inc) and 6 multiaxis force platforms (AMTI Inc). At JAHVH, the Rehabilitation and Biomechanics Laboratory is equipped with a 12-camera motion capture system (Vicon Inc) and 4 multiaxis force platforms (AMTI Inc). The systems track the positions of passive reflective markers at a rate of 120 Hz, and force platforms sample ground reaction forces at a rate of 1200 Hz. Visual3D software (C-Motion Inc) will be used for analysis of 3D motion capture data.

#### Collection of Reliable Gait Data Among Laboratories

A previous interlab reliability study was conducted among gait laboratories at the 3 military treatment facilities, which demonstrated that despite differences in marker configurations, camera systems, and examiners among the sites, reliable gait data were collected across the 3 gait laboratories [49]. A key to similarity among sites was the use of identical anatomical segment definitions for the respective gait models. To reduce variability during data collection, the 3 laboratories in this investigation will implement the key recommendations of the interlab reliability study, including the use of identical anatomical segment definitions. In addition, all 3 sites will use identical marker sets, and a single examiner at each site will conduct postprocessing of the respective data.

#### Kinematic and Kinetic Data Capture

Gait analysis will be performed after each acclimation period during visits 3 to 5. Each participant will be provided biomechanically neutral shoes that offer neither supinatory nor pronatory control. A custom, full-body passive reflective marker set will be placed on each participant, which tracks each segment independently, allowing for the accurate measurement of movements. A total of 78 markers will be placed or digitized on the head, trunk, pelvis, and extremities in the following locations: bilaterally over the positions of the medial and lateral ankle malleoli; lateral and medial condyles of the femur; tibial tuberosity; fibula head; first, third, and fifth metatarsals; anterior superior iliac spine; posterior superior iliac spine; calcaneus; lateral of the calcaneus; jugular notch; xiphoid process; spinous process of the seventh cervical vertebrae and tenth thoracic vertebrae; acromioclavicular joints; right and left scapulae; medial and lateral epicondyles of the humerus; styloid process of the radius and ulna; forearm; third metacarpal; and 4 markers on the head. Marker placements for the prosthetic limb will be matched to those of the intact leg or on centers of rotation. The cluster technique will be used to minimize the surface-to-bone displacements for the thigh-mounted, shank-mounted, and upper arm–mounted markers [50]. As such, tracking clusters will be placed bilaterally on the thigh, shank (tibial crest), and upper arm. Functional joints will also be calculated for the intact ankle and bilaterally for the knees and hips [51].

#### Data Collection Procedure

During each experimental session, participants will walk at 3 speeds across a 4-m instrumented walkway until 5 acceptable trials for each foot are completed. Trials will be considered acceptable when a foot makes full contact with a force platform. As kinetic outcome measures are speed dependent, participants will ambulate at 3 separate, controlled speeds: 1, 1.3, and 1.5 m/s. These speeds were selected to represent slow, moderate, and fast walking speeds for individuals with lower limb loss. The order of speeds will be randomized for each participant for each data collection visit. Auditory feedback will be provided to the participant by the study team to ensure that all participants walk at the targeted speed (–5% to +5%). Participants will be asked to repeat the walking trials until 5 acceptable trials for each foot at each speed are collected.

#### Incline and Decline Ambulation

Participants in this subset will also perform ramp ascent and descent to collect kinematic data during ramp ambulation. This will be performed on a standardized ramp (rise-to-run ratio of 1:6) with a minimum length of 4.9 m to allow for sufficient number of steps to be taken by the participant. Participants will be instructed to ambulate at a comfortable, self-selected walking speed. This will include 5 trials ascending and 5 trials descending the ramp.

### Data Analysis

The reflective marker positions will be digitized using motion tracking software. A 15-segment (head, trunk, pelvis, bilateral upper and lower arms, hands, thighs, shanks, and feet) rigid body model will be created based on the skin-mounted markers and functional joints. Local coordinate systems for each segment will be defined using the International Society of Biomechanics recommendations [52,53]. The data of acceptable walking trials of each participant at each speed will be processed using Visual3D. Marker data will be filtered with a 6-Hz Butterworth low-pass filter. Raw analog data will be filtered using a second-order low-pass Butterworth filter with a 25-Hz cutoff frequency. Visual3D will be used to calculate temporal-spatial values, walking speed, and lower extremity kinematics and kinetics. Inverse dynamic analysis will be applied to the kinematics of the biomechanical model and to the location, magnitude, and direction of ground reaction forces acting on the foot to calculate lower extremity joint torques and powers, including ankle, knee, and hip power of the biological and prosthetic limbs during stance and the frontal plane knee moments for the unaffected limb of participants (30/100, 30%). The resultant ground reaction force will be calculated as the magnitude of the ground reaction force vector. Several parameters, including temporal-spatial variables (eg, step lengths, stance and swing times, cadence, and stride length); peak angles; segment ranges of motion, moments, and powers for the ankles, knees, and hips during each phase of gait; and other biomechanical parameters (eg, external adduction moment rate, impulse external knee adduction moment, peak vertical ground reaction force, and peak resultant ground reaction force) will be measured and statistically compared across all conditions. Means, maximum and minimum values, ranges of motion, SEs, and coefficients of variation will be computed for the values attained per gait cycle over each trial and for each set of trials.

### Statistical Analysis

Across the study population, outcomes will be assessed using descriptive statistics (ie, means and SEs) and compared between each ankle-foot device category. Inferential statistics for ordinal data will be conducted with a repeated-measures Friedman test (α=.05) and a Dunn post hoc test at 95% CI. To identify which measures are the most sensitive to changes in ankle-foot device type, a linear mixed effects model will be used. Separate models will be run for each type of measure (ie, subjective, functional, and biomechanical), and measures that have a significant association with device type in the presence of adjusting or control variables will be determined. In the case of significance, pair-wise comparisons will be tested for significance using linear contrasts with Tukey Honestly Significant Difference or by applying Bonferroni correction. The performance of each device in each test will be ranked, and the arithmetic mode will be used to determine which device is the most suitable for each participant. Adjusting or control variables in the model will include weight, height, etiology, time since limb loss, sex, race, functional level, and current ankle-foot device.

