**Methods:**

This investigation will be a multisite, randomized, crossover clinical trial targeting the enrollment of 100 participants. Participants will use 3 different types of prosthetic devices (energy storing and returning, articulating, and powered) in random order. Participants will be fitted and trained with each device and then separately use each device for a 1-week acclimation period. Following each 1-week acclimation period, participants will be evaluated using several functional measures and subjective surveys. A random subset of participants (30/100, 30%) will also undergo full-body gait analysis, following each 1-week acclimation period, to collect biomechanical data during level ground and incline and decline walking. After all individual device evaluations, participants will be given all 3 prostheses concurrently for 4 weeks of home and community use to capture user preference. Activity monitoring and a guided interview will be used to determine overall user preference.

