### Sample Size Determination and Power Analysis

Sample size determination was based on power analysis of several biomechanical, subjective, and functional measures collected during pilot investigations (Table 2). Assuming an α error rate of 5% and using within-group SDs determined from the pilot investigations, power is provided for selected parameters for a sample size of 100 participants for functional and subjective outcomes and a sample size of 30 for biomechanical parameters.

**Table 2 table2:** Sample size determination and power analysis of selected parameters.

Parameters		Difference, mean (SD)	Power (N=100; subset of 30/100, 30%, where appropriate), %

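### Table 2 gives power at an unadjusted 5%, but device pairs are to be tested with Tukey or Bonferroni after a significance gate, so its figures are not the power of the planned pairwise tests (minor)

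*Protocol article*

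**What the plan says.** The trial is a three-device crossover: "Participants will use 3 different types of prosthetic devices (energy storing and returning, articulating, and powered) in random order". Three devices give three pairs.

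For continuous measures, the Statistical Analysis section fits a linear mixed model and looks first for an association with device type. Pairs come second: "In the case of significance, pair-wise comparisons will be tested for significance using linear contrasts with Tukey Honestly Significant Difference" "or by applying Bonferroni correction". Ordinal data follow a parallel route, a Friedman test and then Dunn.

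The Sample Size Determination and Power Analysis section sets the error rate for Table 2: "Assuming an α error rate of 5% and using within-group SDs determined from the pilot investigations". It gives the powers for "a sample size of 100 participants for functional and subjective outcomes and a sample size of 30 for biomechanical parameters". Each row of Table 2 has one mean difference, one SD and one power. The section names no device pair, test, sidedness or within-person correlation, and no allowance for multiple comparisons.

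**The concern.** A single difference with a single SD describes a two-device contrast. If Table 2 is power for such a contrast at 5%, it describes a more lenient test than the one planned for device pairs. A pair with p between about 0.019 and 0.05 counts as detected in the power calculation and as not detected in the analysis.

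The second layer of correction is also not needed to hold the family-wise error at 5% within a measure. With exactly three devices, any two pairwise null hypotheses together imply that all three devices are equal. A 5% omnibus test followed by each pair at 5% is therefore a closed test.

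The pairwise contrasts show which category does better on a measure, and so bear directly on the objective of developing prescription criteria. Power lost there is worth recovering if it can be done at no cost in error control.

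**Working it through.** **Inputs.** Differences and SDs from Table 2; alpha 5%; n = 100 (functional, subjective) or 30 (biomechanical). Assumed because not stated: two-sided tests, within-person correlation ρ from 0 to 0.5, no dropout.

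**Step 1: what Table 2 computes.** For an unpaired two-sided t-test with n per group, power = P(T > t_crit), where T is noncentral t with 2n − 2 df and noncentrality (difference/SD) × √(n/2). With 30 per group:

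| Row | Difference/SD | Stated | Computed, 5% |
|---|---|---|---|
| PEQ satisfaction | 13.6/12.4 | 98.7 | 98.7 |
| PEQ frustration | 15.9/24.7 | 68.6 | 68.9 |
| PEQ utility | 8.4/8.8 | 95.5 | 95.3 |
| Steps at high activity | 9/13.1 | 74.4 | 74.4 |
| 6-minute walk | 60/61 | 96.3 | 96.3 |
| Ankle range of motion | 2.9/3 | 95.3 | 95.7 |
| Peak plantarflexion | 3.2/3.6 | 91.1 | 92.3 |
| Radius of curvature | 7.3/9.2 | 81.7 | 85.6 |

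A one-sided 5% test does not fit (frustration would be 79.4%). The five functional and subjective rows agree within 0.3 points and radius of curvature misses by about 4. So the table behaves as one two-device contrast at an unadjusted two-sided 5%. The five rows labelled N=100 also fit 30 per group, unpaired. With 100 per group, frustration would be 99.5% and steps 99.8%.

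**Step 2: per-pair alpha in the analysis.** Bonferroni: 0.05/3 = 0.0167. Tukey, from the studentized range with 3 groups and 2(n − 1) df: 0.0194 at n=30 and 0.0192 at n=100.

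**Step 3: power of a paired test at the actual n.** SD of the within-person difference = SD × √(2(1 − ρ)); noncentrality = difference × √n / that SD; n − 1 df. Example, radius of curvature at ρ=0: SD = 9.2 × √2 = 13.01; noncentrality = 7.3 × √30 / 13.01 = 3.07; power 84.4% at 0.05 and 70.1% at 0.0167.

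| Row | n | ρ=0: 0.05 → 0.0167 | ρ=0.5: 0.05 → 0.0167 |
|---|---|---|---|
| Radius of curvature | 30 | 84.4 → 70.1 | 98.7 → 95.8 |
| Peak plantarflexion | 30 | 91.4 → 81.0 | 99.7 → 98.7 |
| Range of motion | 30 | 95.1 → 87.7 | 99.9 → 99.6 |
| PEQ frustration | 100 | 99.5 → 98.2 | 100 → 100 |
| Steps at high activity | 100 | 99.8 → 99.2 | 100 → 100 |

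At ρ=0.25 and alpha 0.0167, radius of curvature has about 84%. Tukey gives up to about 2 points more than Bonferroni. The remaining rows are near 100% throughout.

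**Step 4: is the second correction needed?** Simulated three-device crossovers, n=30, omnibus F at 5% and then each pair at 5%: family-wise error 0.051 with no device differences, 0.049 with one device differing by 0.5 SD, and 0.050 with one differing by 2 SD. Without the gate it is about 12.5% when no devices differ. In the two cases with one device differing, the plan's gated Tukey or Bonferroni rule runs at 0.016 to 0.019.

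**Step 5: what the closed test gains.** Per-pair power, effects in SDs of the paired difference:

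| Scenario | Omnibus, then 5% | + Tukey | + Bonferroni |
|---|---|---|---|
| n=30, one device differs by 0.5 | 72% | 63% | 61% |
| N=100, one device differs by 0.25 | 63% | 54% | 52% |
| N=100, graded steps of 0.25, adjacent pairs | 70% | 56% | 54% |

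The gain is 9 to 16 points. These effect sizes are assumed; the protocol does not give them.

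**The case against.** Three stronger readings are tempting, and the document supports none of them.

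- **That the functional and subjective comparisons are underpowered.** Rerunning the 30-per-group calculation at 0.0167 gives frustration 51.5% and steps 58.0%. Those figures cannot arise in this trial, which is a crossover with N=100 for these outcomes. The adjusted paired tests have at least 98% power, more than the 68.6% and 74.4% stated.
- **That the protocol states two alphas for the same test.** It does not. The power section names no pair or test, and the analysis section gives no per-pair level. A 5% family-wise rate is compatible with a stated error rate of 5%. That Table 2 is per pair is inferred from its layout and from a fit that misses one row.
- **That the planned rule is wrong.** An omnibus test followed by Tukey or Bonferroni is standard and valid, and it supplies simultaneous intervals. Dropping the adjustment is a choice.

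It can also be said that the model's first aim is to find measures sensitive to device type, with pairs as follow-up; that the gait-subset loss rests on an unstated correlation; and that a condensed article may leave the choice between Tukey and Bonferroni to a fuller document. All of this stands and limits the point to a minor one. What remains is that Table 2 has no allowance for the pairwise adjustment, so its figures cannot be read as the power of the pairwise tests. The adjustment also costs power that closed testing would recover.

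**Conclusion.** The point holds in limited form, at minor severity. Table 2 fits one contrast at an unadjusted 5%, while pairs will be tested at about 0.019 or 0.0167 after a gate. For the effects listed, this costs about 7 to 14 points of power in the gait subset at correlation 0, at most about 3 points at correlation 0.5, and about 1 point or less at N=100. For moderate effects below those listed, the closed test would recover 9 to 16 points per pair.

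The alpha gap is not the main fault in Table 2. The larger and separate one is that the rows labelled N=100 reproduce only at about 30 per group, unpaired. No error control fails under the plan as written. The figures assume two-sided tests, normal data, no dropout and correlations between 0 and 0.5.

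**What to change.** Choose one of two.

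(a) In the Statistical Analysis section, replace the Tukey/Bonferroni step with: for each measure whose own omnibus device test is significant at two-sided 5%, each of the three pairwise device contrasts is tested at two-sided 5% (closed test for three devices; family-wise error 5% per measure). Tukey intervals can be shown descriptively. The text must make clear that each measure has its own omnibus test, because it now speaks of separate models by type of measure. The cost is one sentence. The downside is that unadjusted intervals are not simultaneous and may disagree with the Tukey intervals. The gate also keeps a small cost of its own: for radius of curvature at correlation 0, with one device differing, gated testing at 5% gives 81.7%, against 84.4% for an ungated paired test. The change covers only the three pairs within a measure, not the number of measures or the Friedman/Dunn route.

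(b) If Tukey or Bonferroni is kept, restate Table 2 at the per-pair alpha (about 0.019 or 0.0167) for the paired three-device design at the actual n of 100 or 30, using the SD of within-person differences or a stated range of correlations. Changing the alpha alone would leave the wrong design and sample size in the table. The cost is one recalculated column. Neither option needs more participants or data.

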## Methods

### Study Overview

This investigation will be a prospective, multicenter study**,** including 4 sites: Veterans Affairs New York Harbor Healthcare System (VANYHHS), Veterans Affairs Puget Sound Healthcare System, James A Haley Veterans’ Hospital (JAHVH), and Walter Reed National Military Medical Center (WRNMMC). Enrollment began in 2018, and data collection is expected to be completed in 2023. A total of 100 participants will be enrolled from the 4 sites. Briefly, participants will use 3 different types of prosthetic ankle-foot devices (refer to device categorization in the following sections) with duplicate sockets. Participants will be fitted and trained with each device and then separately use each ankle-foot device for a 1-week acclimation period. Participants will only use the assigned study device for each acclimation period. Although previously reported acclimation periods for lower extremity prosthetic device studies have ranged from minutes to months depending on componentry [27-30], this study will use a 1-week acclimation period to balance the time that participants need to adjust to the features of each ankle-foot device with the overall duration of their participation. To augment the acclimation period, device-specific training will be provided to ensure that participants meet a minimum standard of performance. Following each 1-week acclimation period, participants will be evaluated in the laboratory using several functional and subjective measures. Furthermore, a subset of participants (30/100, 30%) will be randomly chosen to undergo a full gait analysis to collect biomechanical data during level ground and incline and decline walking using each ankle-foot device. Following the 3-week data collection period, participants will be given all 3 prostheses at the same time for 30 days to use at home and in their community. Step activity monitoring during home-based and community-based use and a final guided interview will be used to determine overall user preference.

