#### Randomization of Ankle-Foot Device Selection and Order of Evaluation

The ankle-foot devices for each participant and the order in which they will be evaluated will be block randomized using a computer-generated algorithm that randomly selects from all available devices and then assigns the order. The randomization will be performed before study enrollment, so that each combination of device order is used an equal number of times. Investigators who process and evaluate the data will be blinded to the data. Owing to the distinct differences between prosthetic ankle-foot devices, the participants and study prosthetists cannot be blinded to which foot is assigned.

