#### Visits 3 to 5—Functional Assessment of ESR, ART, and PWR Ankle-Foot Devices

Visit 3 will begin after the 1-week acclimation period while using the first assigned ankle-foot device. Participants will complete the VAS pain scale and then a battery of outcome measures and surveys (outlined in the following sections). In addition, during visit 3, a subset of participants will also be randomized to undergo biomechanical gait analysis while using the first prosthesis (described in the following sections). Once visit 3 is completed, the participant will receive the second prosthesis according to the established randomization schedule, and the initial prosthesis will be returned to the study prosthetist. The participant will again complete a 1-week acclimation period. During visit 4, the participant will undergo the same pain scale and battery of outcome measures and surveys. The same subset of participants will also undergo biomechanical gait analysis using the second prosthesis. The third prosthesis will be issued at the end of visit 4, and the second prosthesis will be returned to the study prosthetist. Participants will receive the same 1-week acclimation and will complete the same pain scale and battery of outcome measures and surveys during visit 5. In addition, the same subset of participants will undergo biomechanical gait analysis while using the third prosthesis. For visits 3 to 5, a visit window of –2 to +2 days will be implemented.

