### Development of Prediction Model

To develop evidence-based guidelines for the prescription of prosthetic ankle-foot devices, the goal of this investigation is to determine which factors and outcomes are the most predictive of optimal performance to meet patient goals. To do this, initial analyses will consist of bivariate cross-tabulations, performed using chi-square analyses. Variable selection for the multivariate model will be informed by these bivariate findings. Logistic regression will then be performed with participants’ preference of prosthesis regressed on each of several domains (eg, functional levels and outcomes, activity levels, and biomechanical parameters). The models will simultaneously control for multiple variables, and overall model predictive value will be assessed using the C-statistic. Domain-specific models (based on bivariate findings) and 1 parsimonious stepwise logistic regression model combining the domains will be created to determine whether each distinct component predicts optimal prescription outcome. Each domain-specific model will control for the identified confounding factors. The individual variables of each domain will be used as fixed predictors. Finally, stepwise multiple regression will be used to determine the factors and outcomes that represent the best predictors, which will be conducted through a series of domain-specific, forward regression models. The significant variables in the forward selection models will then be placed in a backward regression model. Significant variables from the backward regression will be considered as the strongest predictive factors and used to develop prosthetic prescription guidelines.

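### The per-participant most-suitable-device label is ranked on one visit per device with no stated correction for visit order, so any trend across visits 3 to 5 can shift it towards the foot tested later

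*Protocol article*

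**What the plan says.** - **Labelling rule (Statistical Analysis).** "The performance of each device in each test will be ranked, and the arithmetic mode will be used", and the stated purpose is "to determine which device is the most suitable for each participant". This gives one label per person.
- **One visit per device (Visits 3 to 5).** "Visit 3 will begin after the 1-week acclimation period while using the first assigned ankle-foot device". For the second device, "During visit 4, the participant will undergo the same pain scale and battery of outcome measures and surveys". The third device follows in the same way at visit 5.
- **Order (Randomization of Ankle-Foot Device Selection and Order of Evaluation).** Orders are block randomized "so that each combination of device order is used an equal number of times". The balance is across participants; each participant has one order.
- **Adjustment (Statistical Analysis).** "Adjusting or control variables in the model will include weight, height, etiology, time since limb loss, sex, race, functional level, and current ankle-foot device". No visit, period or sequence term is named.
- **Acclimation (Study Overview).** One week per device, described as a compromise: "this study will use a 1-week acclimation period to balance the time" needed to adjust against the total length of participation.
- **Prediction model (Development of Prediction Model).** The outcome is the participants' "preference of prosthesis regressed on each of several domains". The label from the ranking rule is not the outcome there.

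**The concern.** The same battery is given three times about a week apart, each time on a different foot. If scores drift upward through familiarity with the tests, continued adaptation or any other time trend, the foot tested later gains. In the group comparison balanced order cancels this. In a label for one person it cannot, because that person supplies only one order.

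Taking the mode over tests does not help where the tests share the trend, since they then err in the same direction. Two people who respond identically to the three feet could receive different labels because they were randomized to different orders. The trial's aim is to set prescription criteria suited to individual patients, so a label that partly reflects visit order would be a poor guide.

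**Working it through.** **1. Can the stated analysis remove a visit trend from the label?** Write the score of participant i on test k with device d as

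Y = participant level + device effect(d) + visit effect(v) + error,

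where v is the visit at which i used d. Each device has one visit and each visit one device, so within a participant the difference between two devices is (device difference) + (visit difference) + error, and the two differences cannot be separated. The listed control variables are participant characteristics. As main effects they add the same constant to all three scores and leave the ranking unchanged. Only a visit term, estimated across participants, could correct it.

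**2. Size.** The article gives no visit effect, so there is no figure of its own to reproduce. Everything below is an assumption range. Simulation set-up: three identical feet, random order, six continuous tests, between-test correlation 0.3 within a visit, constant gain per visit in within-person SD, label = device ranked best in most tests, ties split at random.

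| Gain per visit (SD) | First-tested foot named | Third-tested foot named |
|---|---|---|
| 0 | 33% | 33% |
| 0.05 | 30% | 36% |
| 0.1 | 28% | 39% |
| 0.2 | 22% | 46% |
| 0.3 | 18% | 52% |

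Variants at 0.2 SD per visit:
- Single test instead of the mode of six: third foot 42%. The mode (46%) adds modestly to the shift and does not average it out.
- Half of 12 measures show the trend: 27% first, 40% third.
- 6 of 20 measures show it: 29% first, about 37% third.
- One foot truly better by 0.5 SD on all six tests: correctly named in about 42% if tested first and 66% if tested third.

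**3. The same in metres.** The sample size table gives an SD of 61 m for 6-minute walk distance, described as a within-group SD. With an assumed within-person correlation r, the within-person SD is 61 × √(1 − r): 43.1 m at r = 0.5 and 19.3 m at r = 0.9. A gain of 0.2 SD is then 8.6 m or 3.9 m per visit. Ranking on this test alone, gains of 5, 10 and 20 m per visit give the third-tested foot 38.5%, 43.3% and 53.4% of labels at r = 0.5, and 44.5%, 55.6% and 73.8% at r = 0.9.

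**4. Group averages.** In the same runs each device still receives 33% of labels overall. The order effect is invisible in the totals and acts only on who gets which label.

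**5. Does subtracting visit means repair it?** With six continuous tests, yes. For gains of 0.1 to 0.3 SD of the difference between two visits (0.14 to 0.42 within-person SD, multiplying by √2), the third-visit share returns to 33.2–33.5%. With three continuous and three coarse, ceiling-limited tests at 0.2 SD per visit, it does not if applied to every test:

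| Scores ranked | First-tested foot | Third-tested foot |
|---|---|---|
| Unadjusted | 22–23% | 45% |
| Visit mean subtracted from all six | about 47–68% | about 14–23% |
| Visit mean subtracted from continuous tests only | 29–31% | 36–38% |

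The range reflects the assumed share of three-way ties. A participant with equal scores on all three feet has the tie broken in favour of the first foot once an upward visit mean is removed.

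**The case against.** The strongest reply is that nothing in the article states or implies a visit trend, and some features should reduce one. Participants walk on every prosthesis at dynamic fitting, are trained to a minimum standard before the first period, and use their own current foot in the energy-storing category. This stands as a limit on size. It does not rehearse the test battery, so a trend is not excluded.

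Second, six continuous tests with an equal gain is an unfavourable choice. The Hill and Stair Assessment Indices are rated scales, the Amputee Mobility Predictor is a 21-item instrument, and the battery includes three surveys. This also stands, and the diluted variants show the smaller effect.

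Third, the article does not say that raw scores are ranked, and a visit term could sit in a fuller document. The point nevertheless concerns a rule the article states together with its list of control variables; as stated, none of them can alter a within-person ranking.

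A reader might infer three stronger things that the documents do not support:
- **That order decides the label.** With no trend there is no systematic shift; order can only help to decide it.
- **That the comparison of device categories is biased.** Balanced order protects it.
- **That the prescription guidelines inherit the fault.** The prediction model regresses preference, which the Visit 6 section bases on activity time over 30 days of free choice, and its list of confounders is left open. That the foot worn last might also be favoured in that month is conjecture.

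**Conclusion.** The point holds in conditional form. The stated rule passes any visit trend straight into the individual label, and neither the balanced order nor the listed covariates can remove it. That part follows from the design and needs no assumption.

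The size does rest on assumptions: a common gain per visit, its magnitude, the between-test correlation and the number of measures affected. Across 0.05 to 0.3 SD per visit the gap between third- and first-tested foot runs from about 6 percentage points (36 − 30) to about 34 (52 − 18) when all six tests share the trend, and at 0.2 SD falls to about 8 (37 − 29) when 6 of 20 do. A correction is worth making because it is cheap and the label is meant to be individual.

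**What to change.** - Add visit (period) to the linear mixed models.
- For continuous tests, such as the 6-Minute Walk Test, Timed-Up-and-Go and Four Square Step Test, subtract the estimated visit effect before ranking.
- For ordinal or ceiling-limited scales, such as the Hill and Stair Assessment Indices and the Amputee Mobility Predictor, keep tied scores tied and do not subtract visit means.
- Report the share of labels by visit position as a check. A clear excess at visit 5 would show that order still matters.
- As a secondary step, include each foot's visit position as a covariate in the preference models.

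Cost: slightly more analysis work and no new data, since order is set by the randomization and each assessment has its visit. A residual order effect remains from the ordinal scales, and a common visit term will not remove device-specific learning, for instance if the two unfamiliar feet improve more with time than the participant's own.
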